## Potential adverse events

MRI

There is no evidence that MRI scanning affects pregnancy however we will err on the side of safety and exclude pregnant women and those with known contraindications to MRI scanning. These include metal implants, metallic foreign bodies and pace makers. All potential participants will be carefully screened to ensure no MRI exclusion criteria are present. If the participant has a tattoo they will be advised of the potential for heating of the metallic tattoo dyes which may cause a burn to the skin. They will asked to sign a further consent form to acknowledge they have been advise of the potential problems that can occur with tattoos and are happy to proceed with the scan.

Medical research staff will be present to provide appropriate care in the unlikely event any other adverse event occurs, Adverse events will not be routinely reported to the REC, unless the Chief Investigators requests.

All participants will receive a copy of the standardised participant information sheet which details how to contact the investigators should the need arise. The investigators will be the first contact point for adverse events. However, if the investigators are unavailable, or on advise of the research team, the participant will be asked to contact their GP or Accident and Emergency Department.

# TRANSPORT AND STORAGE OF THE TISSUES AND LABORATORY ANALYSES

Blood samples:

Blood samples which will be processed by the Nottingham University Hospitals Biochemistry laboratory will be labelled with the patients name, date of birth, date of sample taken and NUH hospital number as per standard NHS protocol for blood sample labelling. Trial blood samples for cytokines and adipokines with be separated to collect the serum/plasma and frozen as per the standard operating procedure for these samples. All cryo-tubes will be labelled with the patient initials, date of birth, MRI allocated study number and date the sample was taken.

Samples will be frozen at the Brain and Body centre and transported by a member of the research team to the NDDC laboratories where they will be stored in the NDDC -80oC freezers until processed. Serum/Plasma samples will be transported to the Nottingham City Hospital laboratories for cytokine and adipokines analysis by a member of the research team using standard procedures as advised by [name] team at the Nottingham City Hospital. [name] team will advise and help carry out analysis of the samples.

Participant detail, initials, date of birth, NUH hospital number, MRI number and date of scan will be maintained in a paper version (locked in a filing cabinet in a locked office at the NDDC) and on a password protected Microsoft access database held on the University of Nottingham server. All study documents will be anonymised using the MRI number, initials and date of birth.

Stool Samples

Samples will be collected by the researchers on the MRI study day. The participant will collect 1 stool sample and split it between 3 pots to allow ease of analysis. They will be stored at 4oC (on ice) before being transported by a member of the research team to the NDDC laboratory freezers and frozen at -20oC. All samples will be labelled with the patient initials, date of birth, MRI allocated study number and date the sample was taken. Stool will be analysed for Calprotectin and/or microbiological organisms. In order to accurately identify microbiological organisms, Bacterial DNA may be extracted from stool samples and analysed.

Participants will be asked if they would like to donate their study samples to as yet unspecified future studies at the end of the study. This is optional for the participants. If they would like to donate any remaining samples, they will be asked to sign the corresponding consent form section. Any remaining samples (with consent) will be retained under the UoN HTA licence reference 12265. If they decline, the samples will be taken for the study, but destroyed at the end of the study following the HTA principles.

# STATISTICS

### Methods

Statistical analysis will carried out with the use of Prism 4 (GraphPad Software Inc, San Diego, CA). Comparisons between groups were performed by using 2-tailed unpaired *t* test or the Mann–Whitney's *U* test, for normal and non-normal data respectively by [name] and [name]

### Sample size and justification

No previous studies have used MRI measures of visceral and subcutaneous fat to assess its relationship to symptoms in diverticular disease.

However based on results using abdominal MRI to detect fat distribution by Liou et al in 2006[50], the sample size required to detect a 30% difference in visceral fat between groups with a power of 90% and p<0.05 is 35 participants per group.

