**Obesity and Diverticular disease**

There is increasing evidence that obesity is linked to complications of diverticular disease. In Parks’ 1968 study of colonic specimen, 50% of DD samples had excess fat attached compared to control samples with no noticeable gender difference[15].

More recent epidemiological studies have also suggested an association. In a 5 year retrospective study of 61 patients with diverticulosis, a significant difference in body mass index (BMI) was demonstrated between those with no symptoms and those who developed perforation or recurrent episodes of diverticulitis[16]. In a larger prospective cohort study, a BMI >30kg/m2, high waist circumference and a high waist to hip ratio was shown to significantly increase the relative risk of diverticular bleeding and diverticulitis[17]. Studies of patients under the age of 40yrs with acute diverticulitis have also demonstrated an association with obesity[18]. In addition a correlation between obesity and uncomplicated symptomatic diverticular disease has been found in a Nottingham study[19]

With the prevalence of obesity increasing in westernised populations, the risk of complications from diverticular disease is likely to increase as well. However there is little understanding of how obesity increases diverticular complications.

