## PURPOSE

## Hypotheses

1. DD Patients with a higher proportion of visceral fat will have increased incidence of painful symptoms and loose stool compared to patients with higher subcutaneous fat distribution.
2. Patients with DD symptoms will have decreased levels of adipokines compared non-symptomatic DD controls but have increased levels of circulating pro-inflammatory cytokines.
3. Patients with diarrhoea predominant diverticular disease will show similar MRI results to D-IBS patients, having reduced fasting small bowel water content and a narrower gastrointestinal lumen diameter (contracted small bowel) but increased colonic water.

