## PRIMARY OBJECTIVE

Difference in the volume of visceral fat compared to abdominal subcutaneous fat between symptomatic and asymptomatic DD groups

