# Methods

## Participant groups

We will recruit n = 35 participants in each group (Total 105). Participants will include;

- 1. 35 participants with symptomatic DD and a patient heath questionnaire 15 score of >7
  2. 35 participants with symptomatic DD and a patient heath questionnaire 15 score of <7
  3. 35 participants with asymptomatic DD

The DD groups will be age and sex matched.

Having excluded those with e.g severe co-morbidity, alcoholism or drug dependence or inability to give informed consent (see exclusion criteria), we will invite participation in the MRI study day.

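### The only stated power (90%, 35 per group) is for visceral fat volume, while the primary endpoint is visceral relative to subcutaneous fat, so power for the primary endpoint is not established

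*Protocol*

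**What the plan says.** The Primary Objective, repeated as the primary end-point in the Synopsis, is: "Difference in the volume of visceral fat compared to abdominal subcutaneous fat between symptomatic and asymptomatic DD groups". Hypothesis 1 is also framed in relative terms: "DD Patients with a higher proportion of visceral fat will have increased incidence of painful symptoms and loose stool".

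The Sample size and justification section, repeated in the Synopsis, concerns a different quantity: "the sample size required to detect a 30% difference in visceral fat between groups with a power of 90% and p<0.05". Its answer is 35 participants per group, and it is described as "based on results using abdominal MRI to detect fat distribution" in one cited study. SAT has no part in the effect size, and no SD is given for any fat measure. No other section gives a power statement.

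Under Participant groups there are three groups of 35: two symptomatic groups, split by questionnaire score, and one asymptomatic group. They are matched on age and sex. The Statistics section names a "2-tailed unpaired" t test, or the Mann-Whitney test for non-normal data. It does not say whether the two symptomatic groups are pooled for the primary comparison.

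**The concern.** A measure of VAT relative to SAT has its own SD and its own expected group difference, and neither follows from a 30% difference in VAT. A reader who takes the 90% as the power of the primary test is applying it to a variable it was not calculated for.

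The gap could matter here. The background reports that "a correlation between obesity and uncomplicated symptomatic diverticular disease has been found in a Nottingham study", and the groups are not matched on BMI. It is therefore plausible that SAT is also higher in symptomatic patients, which would shrink any difference in the ratio. In the limiting case both depots are 30% larger: VAT then differs by 30% and VAT/SAT does not differ at all. The two variables can give different answers, so the protocol should say which one carries the primary conclusion and which one the power belongs to.

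**Working it through.** **Inputs from the protocol.** 30% difference in VAT; power 90%; p<0.05; 35 per group; two-sided unpaired t test; three groups of 35.

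**Inputs not in the protocol, so assumed.** SD of VAT (backed out below); SD of SAT (log-SD taken equal to that of VAT); VAT-SAT correlation ρ (0 to 0.7); SAT difference between groups (0, 10, 20 or 30%).

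**Step 1: the plan's own figure.** With no SD given, 35 cannot be reproduced forwards, only solved backwards. For 35 vs 35, two-sided 0.05 and 90% power, the noncentral t distribution gives a standardised difference of d = 0.786 (normal approximation: (1.960 + 1.282) × √(2/35) = 0.775).
- On the raw scale, the implied CV of VAT is 0.30 / 0.786 = 0.382.
- On the log scale, the implied log-SD is ln(1.30) / 0.786 = 0.262 / 0.786 = 0.334.

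So 35 per group is internally possible for VAT with a CV of about 38%. No arithmetic error is shown. If the two symptomatic groups are pooled (70 vs 35), the same VAT effect has about 96% power.

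**Step 2: SD of the relative measure.** Taking ln(VAT/SAT) as one possible form:

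Var = s_V² + s_S² − 2ρ·s_V·s_S. With s_V = s_S = 0.334, SD = 0.334 × √(2 − 2ρ).
- ρ = 0: 0.472
- ρ = 0.5: 0.334
- ρ = 0.7: 0.259

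**Step 3: effect on the relative measure.** If VAT is 30% higher and SAT is higher by a factor k, the effect is ln(1.30/k): 0.262 for k = 1.0, 0.167 for k = 1.1, 0.080 for k = 1.2, and 0 for k = 1.3.

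**Step 4: power (noncentral t, two-sided 0.05), as ρ goes from 0 to 0.7.**

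| SAT in symptomatic patients | 35 vs 35 | 70 vs 35 |
|---|---|---|
| equal | 63-99% | 76-99.8% |
| 10% higher | 31-76% | 40-87% |
| 20% higher | 11-25% | 13-32% |
| 30% higher | no ratio effect | no ratio effect |

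With SAT equal and 35 vs 35, power is 90.0% at ρ = 0.5 and 98.7% at ρ = 0.7. At ρ = 0.5 the log ratio has the same SD as log VAT, so the stated power carries over exactly; above that it is exceeded.

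**Step 5: what could be stated instead.** The ratio of geometric means detectable with 90% power is exp(d × log-SD), where d = 0.786 for 35 vs 35 and 0.677 for 70 vs 35. For a log-SD of 0.259 to 0.472 this gives:
- 35 vs 35: exp(0.786 × 0.259) = 1.23 to exp(0.786 × 0.472) = 1.45
- 70 vs 35: exp(0.677 × 0.259) = 1.19 to exp(0.677 × 0.472) = 1.38

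**The case against.** A reader might infer that the primary endpoint lacks 90% power. The protocol does not support that. It supplies none of the quantities needed, and under the assumptions above the ratio reaches or exceeds 90% when SAT is equal between groups and the depots are at least moderately correlated. This objection stands: the defensible statement is that power is not established.

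The low figures also need care. When SAT is 30% higher there is no ratio difference, so the 5% rejection rate is the type I error rate and not a power shortfall. Hypothesis 1 concerns a shift in proportion between depots, and the 20% scenario removes most of that shift. The background reports a correlation with obesity but no SAT measurement, so the 10, 20 and 30% values are illustrations.

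Pooling the symptomatic groups is arguably the plainer reading of the primary objective and improves every non-null figure. Both allocations are therefore shown.

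The exact derived variable may be fixed in a SAP that is not shown, so it cannot be claimed that it would be chosen after seeing the data. But a SAP cannot make a power figure calculated for VAT apply to another variable; the protocol itself states both and they do not match.

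Finally, this is a single-visit pilot in which both depots are imaged anyway. That lowers the severity. It does not remove the point, because the protocol names a primary endpoint and justifies its size with a formal 90% claim.

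**Conclusion.** The concern holds in a limited form. The 90% power for a 30% difference belongs to VAT volume, the primary endpoint is VAT relative to SAT, and no power is given for the latter. Its power could lie above or below 90%.

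With VAT 30% higher, SAT equal or 10% higher, and both allocations considered, the illustration runs from 31% to 99.8%. With SAT at least 10% higher, every value is below 90% under either allocation. These figures rest on the implied log-SD of 0.334 being right for VAT, the same log-SD for SAT, correlations of 0 to 0.7, and a log-ratio form of the endpoint. None of these is in the protocol.

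The importance is moderate: a stated figure is attached to the wrong variable, in a pilot where all the data needed for either variable will be collected.

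**What to change.** Align the primary variable with the power statement, in one of two ways.

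1. Make VAT volume the primary variable, so that the existing 90%/30% statement applies to it, and list VAT/SAT as the first secondary variable.
2. Keep the relative measure as primary and define it once, for example as ln(VAT/SAT). Say that the 90%/30% statement refers to VAT only. Restate the primary precision as a detectable ratio of geometric means together with its assumed SD: on the assumptions above, about 1.23-1.45 for 35 vs 35 or 1.19-1.38 for 70 vs 35.

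In either case, state whether the primary contrast is 35 vs 35 or the pooled 70 vs 35, and give the SD taken from the cited source so that the 35 can be checked. Make the same change in the Synopsis.

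The cost is protocol wording only, with no additional participants, visits or scans. Whether the restated power is better or worse than 90% cannot be known until an SD and an expected effect for the relative measure are supplied.

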# ETHICAL AND REGULATORY ASPECTS

The Research Ethics Committee approval will be obtained prior to initiation. Similar studies have been performed previously with no ethical problems. No ethical problems are foreseen in this project however there is a risk that we will notice something unexpected on the abdominal scans, although we are taking these scans for scientific research. They are not the same as scans collected by doctors for medical purposes and the images will not be looked at by a radiologist. All biochemical tests will be analysed by an NHS laboratory.

However if we should notice something abnormal on abdominal imaging or in biochemical analysis of blood samples the principal investigator will arrange for a specialist radiologist or other medical professional to examine the scans or blood tests and advise if any further action that should be taken. The research team and/or a medical doctor will explain the situation to the participant and on any further action that should be taken. If the participant agrees, the principal investigator will also contact the participant’s G.P. (as chosen by the participant in the Consent Form to make them aware of any referral or treatment that may be needed.

The analysis used for cytokines and adipokines does not have relevance to current clinical diagnosis or practice. However, if during the study, new information should result in any of our cytokine or adipokines assessments being utilised in clinical practice, the research team will review our study records, gain advice from specialists and assist in contact any participants who may be affected in order to make them aware of any referral or treatment that may be needed.

## ETHICS COMMITTEE AND REGULATORY APPROVALS

The study will not be initiated before the protocol, consent forms and participant and GP information sheets have received approval / favourable opinion from the Research Ethics Committee (REC), and the respective National Health Service (NHS) Research & Development (R&D) department. Should a protocol amendment be made that requires REC approval, the changes in the protocol will not be instituted until the amendment and revised informed consent forms and participant and GP information sheets (if appropriate) have been reviewed and received approval / favourable opinion from the REC and R&D departments. A protocol amendment intended to eliminate an apparent immediate hazard to participants may be implemented immediately providing that the REC are notified as soon as possible and an approval is requested. Minor protocol amendments only for logistical or administrative changes may be implemented immediately; and the REC will be informed.

The study will be conducted in accordance with the ethical principles that have their origin in the Declaration of Helsinki, 1996; the principles of Good Clinical Practice, and the Department of Health Research Governance Framework for Health and Social care, 2005.

## INFORMED CONSENT AND PARTICIPANT INFORMATION

The process for obtaining participant informed consent or assent and parent / guardian informed consent will be in accordance with the REC guidance, and Good Clinical Practice (GCP) and any other regulatory requirements that might be introduced. The investigator or their nominee and the participant or other legally authorised representative shall both sign and date the Consent Form before the person can participate in the study.

The participant will receive a copy of the signed and dated forms and the original will be retained in the Study records. A second copy will be filed in the participant’s medical notes and a signed and dated note made in the notes that informed consent was obtained for the study.

The decision regarding participation in the study is entirely voluntary. The investigator or their nominee shall emphasize to them that consent regarding study participation may be withdrawn at any time without penalty or affecting the quality or quantity of their future medical care, or loss of benefits to which the participant is otherwise entitled. No study-specific interventions will be done before informed consent has been obtained.

The investigator will inform the participant of any relevant information that becomes available during the course of the study, and will discuss with them, whether they wish to continue with the study. If applicable they will be asked to sign revised consent forms.

If the Consent Form is amended during the study, the investigator shall follow all applicable regulatory requirements pertaining to approval of the amended Consent Form by the REC and use of the amended form (including for ongoing participants).

## RECORDS

### Study Forms

Each participant will be assigned a study identity code number, for use on study forms, other study documents and the electronic database. The documents and database will also use their initials (of first and last names separated by a hyphen or a middle name initial when available), date of birth (dd/mm/yy), date of scan and MRI volunteer code (as allocated by [name] at the SPMMRC). This 4 point identifier will reduce risk of errors linking participant information and MRI findings.

Study forms will be treated as confidential documents and held securely in accordance with regulations. The investigator will make a separate confidential record of the participant’s name, date of birth, local hospital number or NHS number, and Participant Study Number, to permit identification of all participants enrolled in the study, in case additional follow-up is required.

Study forms shall be restricted to those personnel approved by the Chief or local Investigator and recorded as such in the study records.’

All paper forms shall be filled in using black ballpoint pen. Errors shall be lined out but not obliterated by using correction fluid and the correction inserted, initialled and dated.

The Chief or local Investigator shall sign a declaration ensuring accuracy of data recorded in the study.

Monitoring of study data shall include confirmation of informed consent; source data verification; data storage and data transfer procedures; local quality control checks and procedures, back-up and disaster recovery of any local databases and validation of data manipulation. The Chief Investigator, or where required, a nominated designee, shall carry out monitoring of study data as an ongoing activity.

Data entries will be verified by inspection against the source data. A sample (10%) will be checked on a regular basis for verification of all entries made. In addition the subsequent capture of the data on any study databases will be checked. Where corrections are required these will carry a full audit trail and justification.

Study data and evidence of monitoring and systems audits will be made available for inspection by the regulatory authority as required.

### Source documents

Source documents shall be filed at the investigator’s site and may include but are not limited to, consent forms, study records and questionnaires, field notes and MRI images. A Study form may also completely serve as its own source data. Only study staff shall have access to study documentation other than the regulatory requirements listed below.

### Direct access to source data / documents

The study form and all source documents shall made be available at all times for review by the Chief Investigator, Sponsor’s designee and inspection by relevant regulatory authorities.

## *RECORD RETENTION AND ARCHIVING*

In compliance with the DH Research Governance Framework guidelines, the Human Tissue Act and in accordance with the University of Nottingham Research Code of Conduct, the Chief Investigator will maintain all records and documents of the study. These will be retained for at least 7 years or for longer if required. If the responsible investigator is no longer able to maintain the study records, a second person will be nominated to take over this responsibility.

The study documents held by the Chief Investigator on behalf of the Sponsor shall be finally archived at secure archive facilities at the University of Nottingham. This archive shall include all study databases and associated meta-data encryption codes.

## DATA PROTECTION

All study staff and investigators will endeavour to protect the rights of the study’s participants to privacy and informed consent, and will adhere to the Data Protection Act, 1998. The CRF will only collect the minimum required information for the purposes of the trial. CRFs will be held securely, in a locked room, or locked cupboard or cabinet. Access to the information will be limited to the trial staff and investigators and any relevant regulatory authorities (see above). Computer held data including the study database will be held securely and password protected. All data will be stored on a secure dedicated web server. Access will be restricted by user identifiers and passwords (encrypted using a one way encryption method).

Information about the study in the participant’s medical records / hospital notes will be treated confidentially in the same way as all other confidential medical information.

Electronic data will be backed up every 24 hours to both local and remote media in encrypted format.

